## Abstract

**Background:**

Spinal cord injury (SCI) affects 15.4 million people worldwide, with a substantial proportion of incomplete SCI patients remaining non-ambulatory, highlighting the importance of motor function recovery and mobility in rehabilitation. While transcutaneous spinal cord stimulation (tSCS) has emerged as a promising non-invasive neuromodulation technique for enhancing motor recovery, the therapeutic potential of combining tSCS with transcranial magnetic stimulation (TMS) remains largely unexplored. This combination may leverage the complementary mechanisms of supraspinal and spinal neuromodulation to enhance corticospinal tract plasticity and functional motor outcomes.

**Objective:**

To evaluate the efficacy and safety of combined TMS-tSCS intervention compared to tSCS alone for improving lower extremity motor function in individuals with chronic incomplete spinal cord injury.

**Methods:**

This prospective, randomized, controlled, assessor-blinded clinical trial will enroll 60 participants with chronic (>12 months post-injury) incomplete spinal cord injury (AIS C or D) aged 18–65 years from Alexandra Hospital, Singapore. Participants will be randomized 1:1 to receive either combined TMS-tSCS (intervention group) or tSCS with sham TMS (control group) for 16 weeks (32 sessions). The primary outcome is change in Lower Extremity Motor Score (LEMS) from baseline to 16 weeks. Secondary outcomes include walking speed (10-Meter Walk Test), functional independence (Spinal Cord Independence Measure-III), spasticity (Modified Ashworth Scale), electromyography of the lower limb muscles and neurophysiological measures of corticospinal excitability.

**Expected outcomes:**

We hypothesize that combined TMS-tSCS will yield superior improvements in LEMS (≥2 points greater improvement) compared to tSCS alone, with enhanced corticospinal tract plasticity as evidenced by neurophysiological measures.

**Clinical trial registration:**

ClinicalTrials.gov, identifier: NCT07595497.

## Introduction

1

### Background and rationale

1.1

Spinal cord injury (SCI) is a neurological disorder that disrupts motor, sensory, and autonomic functions, with about 15.4 million people affected worldwide as of 2021 (World Health Organization, 2024). Despite the retention of some neural pathways below the level of injury, a substantial proportion of patients with incomplete SCI remain non-ambulatory or dependent on mobility aids in the chronic phase (van Silfhout et al., 2017; van Hedel, 2009), making gait recovery a key rehabilitation priority (Anderson, 2004). The preservation of some neural pathways in incomplete SCI (iSCI) provides a biological substrate for interventions aimed at enhancing neuroplasticity and functional recovery. Among the most disabling consequences of iSCI is lower limb motor impairment, which fundamentally affects mobility, independence, and quality of life (Ahuja et al., 2017).

Traditional rehabilitation approaches for iSCI, including physical therapy, occupational therapy, and locomotor training, remain the cornerstone of post-injury care, although recovery trajectories vary substantially depending on injury severity, completeness, and individual neurological profile (Scivoletto et al., 2004; Burns et al., 2017). While these interventions remain essential components of comprehensive SCI rehabilitation, neuromodulation is increasingly being integrated alongside conventional therapy in specialist SCI rehabilitation centers. Published evidence demonstrates that tSCS delivered concurrently with task-specific activities such as assisted stepping, standing exercises, and gait training can augment the neuroplastic potential of preserved neural circuits and produce functional gains beyond those achieved with conventional therapy alone (Tefertiller et al., 2022; Comino-Suárez et al., 2025). Neuromodulation approaches aim to augment endogenous repair mechanisms by modulating neuronal excitability and promoting activity-dependent plasticity within residual corticospinal and propriospinal pathways (Taccola et al., 2018).

Transcutaneous spinal cord stimulation (tSCS) has emerged as a particularly promising non-invasive neuromodulation technique for SCI rehabilitation. This approach delivers electrical stimulation through surface electrodes positioned over the spine, targeting the posterior roots of the spinal cord, engaging spinal rhythm-generating networks and enhancing the excitability of motor circuits below the level of injury (Minassian et al., 2016). Seminal work by Gerasimenko et al. demonstrated that multisite tSCS could initiate and modulate locomotor circuitry output and induce coordinated stepping movements in non-injured humans, revealing the capacity of transcutaneous stimulation to engage spinal locomotor networks (Gerasimenko et al., 2015). Subsequent studies have confirmed the feasibility and preliminary efficacy of tSCS for improving motor function, standing ability, and walking parameters in in individuals with neurological conditions; notably, Hofstoetter et al. (2021) demonstrated these effects in individuals with multiple sclerosis, while Taccola et al. (2018) reviewed evidence of tSCS-mediated volitional recovery in SCI (Hofstoetter et al., 2021; Taccola et al., 2018). Recent systematic evidence demonstrates that tSCS modulates both spinal and corticospinal excitability, with studies showing decreased H-reflex amplitudes following alternating current tSCS, and increased motor evoked potential amplitudes following direct current tSCS, indicating enhanced neuroplasticity at multiple levels of the motor system (Tajali et al., 2024).

The mechanisms underlying tSCS-mediated motor recovery are thought to involve multiple physiological processes. First, tSCS may enhance the excitability of spinal interneuronal networks, effectively lowering the threshold for activation of motor neuron pools below the level of injury (Taccola et al., 2018). Second, repeated stimulation may induce long-term potentiation-like changes in spinal circuits, strengthening synaptic connections within preserved neural pathways (Tajali et al., 2024). Third, tSCS may engage spinal interneuronal circuits and rhythm-generating networks by providing tonic excitatory input through posterior root afferents, thereby augmenting motor output in response to step-related sensory feedback (Minassian et al., 2016). Recent evidence demonstrates that combined tSCS with activity-based therapy yields clinically meaningful functional gains. Suggitt et al. demonstrated the safety and real-world feasibility of delivering tSCS combined with activity-based therapy across 120 sessions over approximately one year in a community SCI rehabilitation setting, with no device-related adverse events and acceptable tolerability throughout, supporting the viability of prolonged tSCS protocols outside specialist inpatient centres (Suggitt et al., 2025).

While tSCS primarily targets spinal-level circuitry, the integrity and excitability of supraspinal motor centers also play critical roles in motor recovery following iSCI. The motor cortex undergoes substantial reorganization following SCI, with changes in cortical excitability, motor map representation, and intracortical inhibitory-excitatory balance (Nardone et al., 2013; Freund et al., 2011).

Transcranial magnetic stimulation (TMS), a non-invasive technique that induces electrical currents in cortical tissue through electromagnetic induction, is capable of modulating cortical excitability in a frequency-dependent manner, with high-frequency stimulation generally increasing and low-frequency stimulation decreasing excitability (Rossini et al., 2015). Repetitive TMS (rTMS) protocols have shown promise for augmenting motor function in various neurological conditions, including stroke and multiple sclerosis (Lefaucheur et al., 2020). In the context of SCI, preliminary studies suggest that high-frequency rTMS applied to the motor cortex can enhance corticospinal excitability and may improve motor outcomes when combined with physical rehabilitation (Benito et al., 2012; Kumru et al., 2016; Wang et al., 2023). Recent evidence also supports these findings, with randomized controlled trials demonstrating that intermittent theta burst stimulation (iTBS) combined with conventional physiotherapy significantly improveswalking speed, stride length, and functional independence measures in iSCI populations; specifically, Feng et al. (2023) reported LEMS 21.7 → 32.6 in pilot subacute iSCI RCT, while Shi et al. (2025) showed in prospective study (n=138) that 9-week iTBS gave significantly greater improvements, effective rate 86.96% (Feng et al., 2023; Shi et al., 2025). However, while both Benito et al. (2012) and Kumru et al. (2016) demonstrated significant LEMS improvements with rTMS combined with gait rehabilitation, the benefits of rTMS may be limited without concurrent physical training, as cortical neuromodulation alone cannot fully compensate for impaired corticospinal transmission through damaged spinal pathways (Benito et al., 2012; Kumru et al., 2016).

The theoretical rationale for combining TMS and tSCS rests on the principle of convergent neuromodulation, whereby simultaneous or temporally coordinated stimulation of multiple nodes within the motor system may produce synergistic effects that exceed the sum of individual interventions (Barss et al., 2022). By enhancing both cortical motor drive (via TMS) and spinal circuit excitability (via tSCS), combined stimulation may optimize conditions for activity-dependent plasticity throughout the corticospinal axis. This approach aligns with emerging evidence that multi-level neuromodulation strategies may be necessary to maximize functional recovery in complex neurological conditions (Barss et al., 2022).

Despite the compelling theoretical framework, rigorous clinical evidence evaluating combined TMS-tSCS for lower limb rehabilitation in chronic iSCI remains limited. To our knowledge, no randomized controlled trials have systematically compared the efficacy of combined TMS-tSCS against tSCS alone using standardized motor outcome measures. This gap limits our current understanding of whether combining cortical and spinal neuromodulation offers any advantage over spinal stimulation alone. The present protocol is designed as an initial step toward addressing this question, specifically whether adding TMS to tSCS produces greater improvements in lower extremity motor function than tSCS alone. A full characterization of the therapeutic value of this combined approach will require convergent evidence from multiple trials examining different populations, stimulation parameters, and outcome domains.

### Study objectives

1.2

The primary objective of this study is to evaluate whether combined TMS-tSCS yields superior improvements in lower extremity motor function, as measured by the Lower Extremity Motor Score (LEMS), compared to tSCS alone in individuals with chronic incomplete spinal cord injury.

Secondary objectives include:

To compare changes in walking speed and endurance between treatment groups.To assess differences in functional independence outcomes between groups.To evaluate the effects of combined stimulation on spasticity.To characterize neurophysiological changes in corticospinal excitability.To assess the safety and tolerability of combined TMS-tSCS.

### Hypotheses

1.3

**Primary Hypothesis:** Participants receiving combined TMS-tSCS will demonstrate significantly greater improvement in LEMS from baseline to 16 weeks compared to participants receiving tSCS with sham TMS, with a hypothesized between-group difference of at least two points.

**Secondary Hypothesis:** Combined TMS-tSCS will produce greater improvements in walking speed, functional independence, and corticospinal excitability, defined as increases in MEP amplitude, decreases in MEP latency, and/or reductions in motor threshold of the tibialis anterior muscle, compared to tSCS alone, with sustained effects at 4-week follow-up.

## Methods

2

### Study design

2.1

This is a prospective, parallel-group, randomized, controlled, assessor-blinded clinical trial. The study will be conducted at two academic medical centers in Singapore: National University Hospital (NUH) and Alexandra Hospital. Both sites specialize in spinal cord injury rehabilitation and have established neuromodulation research programs. The trial design adheres to the Standard Protocol Items: Recommendations for Interventional Trials (SPIRIT) guidelines and the Consolidated Standards of Reporting Trials (CONSORT) statement for reporting parallel group randomized trials (Chan et al., 2013).

Participants will be randomly allocated in a 1:1 ratio to either the intervention group (combined TMS-tSCS) or the control group (sham TMS plus tSCS). The intervention period will span 16 weeks, with assessments conducted at baseline, 8 weeks (mid-intervention), 16 weeks (post-intervention), and 20 weeks (4-week follow-up; Figure 1). This design allows evaluation of both the immediate effects of the intervention and the durability of any observed benefits.

**Figure 1 F1:**
[figure not shown]
CONSORT flow diagram of the randomized controlled trial comparing combined TMS-tSCS vs. tSCS alone for lower limb rehabilitation in chronic incomplete spinal cord injury. Participants are randomized 1:1 to intervention (combined iTBS + tSCS) or control (sham TMS + tSCS) groups, with assessments at baseline, Week 8, Week 16, and Week 20. AIS, American Spinal Injury Association Impairment Scale; EMG, electromyography; iTBS, intermittent theta burst stimulation; ITT, intention-to-treat; LEMS, Lower Extremity Motor Score; MAS, Modified Ashworth Scale; MEP, motor evoked potential; SCIM-III, Spinal Cord Independence Measure-III; tSCS, transcutaneous spinal cord stimulation; TMS, transcranial magnetic stimulation; 6MWT, 6-Minute Walk Test; 10MWT, 10-Meter Walk Test.

### Study population

2.2

Participants will be recruited from the rehabilitation departments at National University Hospital and Alexandra Hospital, Singapore. Recruitment strategies will include physician referrals, review of electronic medical records for potentially eligible patients, and outreach through spinal cord injury support groups and community organizations in Singapore.

A baseline LEMS threshold of >10 was selected to ensure participants retained sufficient residual motor function to engage meaningfully with the rehabilitation protocol and to demonstrate measurable changes on motor and walking outcome measures. This threshold corresponds to at least some volitional movement in multiple lower extremity muscle groups, which is a prerequisite for task-specific training during tSCS sessions (Table 1).

**Table 1 T1:** Eligibility criteria.

Inclusion criteria	Exclusion criteria
1. Age 18–65 years at enrollment	1. History of seizures or epilepsy
2. Chronic traumatic SCI (≥12 months post-injury)	2. Implanted electronic devices (pacemaker, cochlear implant, DBS, and spinal cord stimulator)
3. Incomplete injury (AIS grade C or D)	3. Metallic implants in head or spine
4. Neurological level of injury C2–L1	4. Pregnancy or planned pregnancy
5. Baseline LEMS > 10 points	5. Active psychiatric disorder or cognitive impairment
6. Medically stable	6. Concomitant neurological conditions (stroke, TBI, neuropathy)
7. Able to provide informed consent	7. Skin breakdown at electrode sites
8. Able to commit to full study duration	8. Current participation in another trial
9. Able to attempt the 10-Meter Walk Test and 6-Minute Walk Test with or without assistive devices and standby assistance	9. History of skull surgery or craniotomy
	10. Medications altering cortical excitability (within 2 weeks)

SCI, Spinal Cord Injury; AIS, American Spinal Injury Association Impairment Scale; LEMS, Lower Extremity Motor Score; DBS, Deep Brain Stimulator; TBI, Traumatic Brain Injury.

### Sample size calculation

2.3

Sample size was calculated based on the primary outcome of change in LEMS from baseline to 16 weeks. Studies of high-frequency rTMS in chronic incomplete SCI have demonstrated LEMS improvements ranging from 1.3 to 4.8 points (Benito et al., 2012; Kumru et al., 2016). Using a conservative estimate of SD = 4.5 points and targeting a clinically meaningful between-group difference of two points (approximately 6% of the total LEMS scale), we calculated the required sample size using a two-tailed independent samples *t*-test with α = 0.05 and power = 0.80.

The calculation yields, *n* = 24 participants per group. Accounting for an anticipated 20% dropout rate based on similar trials in the SCI population, we will enroll 30 participants per group (*N* = 60 total). This sample size also provides adequate power (>0.75) to detect moderate effect sizes (*d* = 0.65) for key secondary outcomes.

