### Primary outcome

3.1

The primary outcome measure is change in Lower Extremity Motor Score (LEMS) from baseline to Week 16, the immediate post-intervention timepoint (Table 3). Week 16 was selected as the primary endpoint because it captures the maximal cumulative effect of the combined neuromodulation protocol following completion of all 32 sessions, aligns with established convention in TMS and tSCS rehabilitation trials (Benito et al., 2012; Kumru et al., 2016; Feng et al., 2023; Shi et al., 2025), and minimizes confounding from post-intervention behavioral variability (e.g., changes in physical activity or unsupervised practice) that may differentially affect the two arms during follow-up. Week 20 is retained as a pre-specified secondary time-point to assess durability of treatment effects within the MMRM framework (Section 5.3).

**Table 3 T3:** Summary of outcome measures.

Outcome	Type	Measurement tool	Clinical significance
Lower extremity motor score	Primary	ISNCSCI (0–50 points)	MCID: 2–3 points; predicts ambulation
Walking speed	Secondary	10MWT (m/s)	MCID: 0.15 m/s
Walking endurance	Secondary	6MWT (meters)	MCD: 45.8 meters; MCID estimates range 30–50 meters
Functional independence	Secondary	SCIM-III (0–100)	Comprehensive SCI-specific measure
Quality of life	Secondary	EQ-5D-5L	Health utility index and EQ-VAS; validated in SCI populations
Spasticity	Secondary	Modified Ashworth Scale (0–4)	Clinician-rated muscle tone
Corticospinal excitability	Exploratory	MEP amplitude/latency	Neurophysiological plasticity marker
EMG	Exploratory	EMG activity	Muscle activity/recruitment

ISNCSCI, International Standards for Neurological Classification of Spinal Cord Injury; 10MWT, 10-Meter Walk Test; 6MWT, 6-Minute Walk Test; SCIM-III, Spinal Cord Independence Measure-III; MEP, Motor Evoked Potential; MCID, Minimal Clinically Important Difference.

The LEMS is a component of the International Standards for Neurological Classification of Spinal Cord Injury (ISNCSCI), representing the summed strength of five key muscle groups in each lower extremity (hip flexors, knee extensors, ankle dorsiflexors, great toe extensors, and ankle plantarflexors), graded on a 0–5 scale for each muscle group. The total LEMS ranges from 0 to 50 points, with higher scores indicating greater motor strength (Kirshblum et al., 2011).

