Potential limitations of this study include the relatively modest sample size, which constrains our ability to detect treatment effects in subgroup analyses. Additionally, while assessor blinding is maintained, participant blinding to TMS is imperfect, potentially introducing expectation effects. We have attempted to minimize this through use of the validated sham procedure and by asking participants not to discuss their perceived treatment assignment.

An important design limitation is the absence of a sham-tSCS control arm or a rehabilitation-only control group. Both arms receive active tSCS, meaning the study cannot isolate the specific contribution of tSCS itself from non-specific or placebo effects. This is particularly relevant given emerging evidence from recent trials suggesting that differences in functional recovery between active tSCS and sham-tSCS groups may be smaller than initially anticipated, as observed in tSCS trials including Comino-Suárez et al. (2025), who found no significant between-group differences at end of intervention period despite follow-up trends favouring tSCS (Kumru et al., 2016). The current two-arm design was chosen pragmatically to focus on the added value of cortical neuromodulation (TMS) over spinal stimulation alone. Future factorial or three-arm designs incorporating a sham-tSCS group and/or a rehabilitation-only control would be needed to fully disentangle the contributions of each intervention component.

If this trial demonstrates superior efficacy of combined TMS-tSCS over tSCS alone, it would support the development of multi-level neuromodulation protocols for SCI rehabilitation and provide a foundation for future studies examining optimal stimulation parameters, treatment duration, and combination with task-specific training. Conversely, a negative result would provide valuable information about the limitations of this approach and redirect research efforts toward alternative strategies.

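### The stated sample-size inputs (2 points, SD 4.5, two-sided 5%, 80% power) require 81 evaluable participants per group, not 24; on those inputs the unadjusted t-test has about 33% to 39% power

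*Protocol article*

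**What the plan says.** Section 2.3 (Sample size calculation) ties the calculation to the primary endpoint: "Sample size was calculated based on the primary outcome of change in LEMS from baseline to 16 weeks". It gives the spread ("Using a conservative estimate of SD = 4.5 points") and the effect: "targeting a clinically meaningful between-group difference of two points (approximately 6% of the total LEMS scale"). The test is a two-tailed independent-samples t-test with alpha 0.05 and power 0.80. The result is stated as "The calculation yields, *n* = 24 participants per group", raised to 30 per group (60 in total) for 20% dropout. The section adds that this size gives power above 0.75 for d = 0.65 on key secondary outcomes.

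Section 1.3 (Hypotheses) uses the same effect: "with a hypothesized between-group difference of at least two points". Section 3.1 (Primary outcome) gives the scale: "The total LEMS ranges from 0 to 50 points". Section 5.2 (Primary analysis) plans an ANCOVA with baseline LEMS, AIS grade, neurological level and site as covariates, at two-sided alpha 0.05. Section 7 (Discussion) says that "a negative result would provide valuable information about the limitations of this approach".

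**The concern.** Every input to the calculation is printed in Section 2.3, so the stated result can be checked directly, and it is too small by a factor of more than three. The 80% power claim belongs to the trial's primary test. The two-point effect is both the primary hypothesis and the lower end of the clinically important range of 2–3 points in Table 3. If power for that effect is well under one half, a non-significant result is the more likely outcome even when the hypothesised benefit is real. Readers are not warned of this: the limitations paragraph in Section 7 links the modest sample size only to subgroup analyses.

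**Working it through.** **Inputs (Section 2.3).** Difference 2 points; SD of change 4.5; two-sided alpha 0.05; power 0.80; 1:1 allocation; dropout 20%.

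**Attempt to reproduce 24 per group.**
- Standardised difference: d = 2/4.5 = 0.444.
- Normal approximation: n = 2 × (1.960 + 0.842)² / d² = 2 × 7.849 / 0.1975 = 79.5, so 80 per group.
- Exact (noncentral t): 80.4, so 81 per group.
- Enrolment with 20% dropout: 81/0.8 = 101.25, so 102 per group, 204 in total.
- The plan's own dropout step is right (24/0.8 = 30). The fault lies in the 24.

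**Other readings of the inputs.** None gives 24.

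| Reading | n |
|---|---|
| One-sided test | 64 per group |
| Paired or one-sample formula | 42 |
| One-sided paired formula | 33 |
| 3-point difference (6% of 50), SD 4.5 | 37 per group |

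**What 24 per group would need.** 80% power at n = 24 requires d = 0.826. That is 0.826 × 4.5 = 3.7 points at SD 4.5, or an SD of 2/0.826 = 2.42 for two points. Neither figure appears in the article.

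**Power under the stated inputs, unadjusted t-test (exact).**

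| Evaluable per group | Power for 2 points | Difference with 80% power |
|---|---|---|
| 24 | 0.326 | 3.7 points |
| 30 | 0.395 | 3.3 points |

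**Effect of the planned ANCOVA.** If covariates explain a share R² of the variance of change, the residual SD is 4.5 × √(1 − R²). The article gives no R².
- With R² = 0.30 (an assumption), the residual SD is 4.5 × √0.70 = 3.76. Power is then 0.44 at 24 per group and 0.53 at 30.
- To restore 80% at 24 per group, the residual SD must fall to 2.42, so R² = 1 − (2.42/4.5)² = 0.71.

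**SD read as cross-sectional.** If 4.5 were the SD of LEMS at one time point, the SD of change would be 4.5 × √(2(1 − r)). A baseline-to-week-16 correlation of r = 0.85 gives SD 2.46 and n of about 25. The article states no correlation and ties the calculation to change.

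**The two other figures in Section 2.3.**
- 2/50 = 4%. About 6% of the scale would be 3 points.
- Power for d = 0.65 (exact t): 0.60 at 24 per group and 0.70 at 30. Both are below the stated 0.75.

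**The case against.** The strongest reply is that Section 2.3 is not how the trial will be analysed. The primary analysis is an ANCOVA on four covariates in the ITT population with multiple imputation, and the SD is described as conservative. This stands as a limit on what may be said. A reader might infer that the trial simply has 33% power. The article does not support that as a flat statement, because the figure holds for an unadjusted t-test, a true SD of 4.5 and 24 evaluable per group. It is not a defence of the 24: the section names the t-test, uses no variance reduction, and would need about 71% of the variance explained.

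A reader might also infer that an observed difference of exactly two points could never be significant at this size. For the unadjusted t-test at SD 4.5 it would not be (p = 0.13 at 24 per group, 0.09 at 30). With the assumed R² of 0.30 and all 30 per group retained, however, the standard error is 3.76 × √(2/30) = 0.97 and p is about 0.044. The inference therefore fails in general.

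Third, Section 7 does not claim that a negative result would exclude a two-point benefit; it says only that such a result would be informative about the approach's limits. Section 5.2 also already commits to an adjusted difference with a 95% confidence interval. Both points are fair. What is missing is the caution about non-significance, given the true power.

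Finally, the article does not show which input is wrong. The 6% figure may point to an intended 3-point difference, although that still needs 37 per group.

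**Conclusion.** The stated sample size is wrong as written: the printed inputs require 81 evaluable per group, not 24. On those inputs, and for the test named in Section 2.3, power for two points is about 33% (24 per group) to 39% (30 per group) against the stated 80%. ANCOVA could improve this, to about 44% to 53% if covariates explain an assumed 30% of the variance, which is still far short. The 6% and the above-0.75 figures in the same section are also wrong. The arithmetic rests only on figures in the article. The ANCOVA range rests on an assumed R², and the intended inputs remain unknown.

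**What to change.** 1. The sponsor should identify which input was intended (the difference, the SD of change, or a variance reduction from covariates) and state it with its source.
2. If two points and SD 4.5 stand, keep N = 60 and restate Section 2.3, for example: with SD 4.5 and an unadjusted two-sided t-test at 5%, power for a two-point difference is about 33% with 24 evaluable per group and 39% with 30; power of 80% is reached at 3.7 and 3.3 points respectively. Any gain claimed from ANCOVA needs a stated and sourced R².
3. Reconcile the 6% with the two-point difference (two points is 4% of the scale).
4. Correct the secondary-outcome claim for d = 0.65 to about 0.60 (24 per group) or 0.70 (30 per group).
5. In Section 7, add that a non-significant result does not by itself exclude a two-point benefit and must be read from the 95% confidence interval of the adjusted difference.

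The abstract and the hypotheses in Section 1.3 need no change on this account. The cost is protocol wording and a less favourable power statement; no extra participants are needed for the restatement. Keeping the claim of 80% power for two points at SD 4.5 with the t-test would instead take 102 enrolled per group, 204 in total.

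### The stated power above 0.75 at d = 0.65 for key secondary outcomes does not follow from the plan's own inputs: it is 0.60 with 24 per group and 0.70 with 30

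*Protocol article*

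**What the plan says.** Section 2.3 (Sample size calculation) describes one method: "we calculated the required sample size using a two-tailed independent samples" t-test "with α = 0.05 and power = 0.80". It reports the result as "The calculation yields, *n* = 24 participants per group". It then allows for dropout: "Accounting for an anticipated 20% dropout rate based on similar trials in the SCI population, we will enroll 30 participants per group", 60 in total. The secondary claim follows directly: "This sample size also provides adequate power (>0.75) to detect moderate effect sizes (*d* = 0.65) for key secondary outcomes".

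No separate test, significance level, sidedness, correlation or variance reduction is given for the secondary figure. Section 5.3 plans ANCOVA for 10MWT, 6MWT, SCIM-III and MAS, with MMRM for the repeated measurements, but gives no design assumption for them.

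**The concern.** A power statement with a named effect size can be recomputed, and this one looked too high for groups of 24 to 30. It matters because the sentence tells readers that the secondary comparisons are adequately powered. Walking speed, functional independence and corticospinal excitability carry the secondary hypothesis in Section 1.3. If that hypothesis is not supported, a reader who relies on Section 2.3 would take a non-significant result as fair evidence against an effect of 0.65 standard deviations. The Discussion does not correct this: it mentions the modest sample size only as a limit on the subgroup analyses.

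**Working it through.** **Inputs (all from Section 2.3 unless noted).** Effect size d = 0.65; two-sided α = 0.05; independent-samples t-test; 24 evaluable per group; 20% dropout; 30 enrolled per group; 1:1 allocation (Section 2.4).

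**Step 1: the dropout inflation.** 24 / (1 − 0.20) = 30 per group. This reproduces, so the two candidate sizes are 24 (evaluable) and 30 (enrolled, nobody lost).

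**Step 2: power at d = 0.65.** For n per group, the t statistic has 2n − 2 degrees of freedom and noncentrality d·√(n/2). Power is the probability that its absolute value exceeds the two-sided 5% critical value.

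| n per group | df | Noncentrality | Critical t | Power (t) | Power (normal approximation) |
|---|---|---|---|---|---|
| 24 | 46 | 0.65 × √12 = 2.252 | 2.013 | 0.597 | 0.615 |
| 30 | 58 | 0.65 × √15 = 2.517 | 2.002 | 0.697 | 0.711 |

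The claim of more than 0.75 is not reproduced at either size. The shortfall is about 15 percentage points at 24 per group and about 5 at 30. The choice between the exact and approximate formula moves the result by less than 2 points, so this is not rounding.

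**Step 3: what would give 0.75.**
- At d = 0.65, 33 per group gives 0.739 and 34 gives 0.752, so 34 evaluable per group are needed.
- At 24 per group, the effect detectable with power 0.75 is d = 0.777, or 0.78.
- At 30 per group, it is d = 0.692, or 0.69.

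**Step 4: could another basis explain the figure?**
- *One-sided test at 5%.* Power is 0.717 at 24 per group and 0.800 at 30. Only a one-sided test with no dropout clears 0.75, and both conditions contradict Section 2.3.
- *ANCOVA, with d on the SD of the outcome itself.* The effective effect is d/√(1 − ρ²), where ρ is the baseline-to-outcome correlation. The article gives no ρ, so a range is shown as an assumption.

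| ρ | Power, 24 per group | Power, 30 per group |
|---|---|---|
| 0 | 0.597 | 0.697 |
| 0.35 | 0.653 | 0.753 |
| 0.50 | 0.721 | 0.816 |
| 0.55 | 0.752 | 0.842 |
| 0.70 | 0.870 | 0.934 |

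The claim is met from ρ of about 0.55 at 24 per group, or about 0.35 at 30 per group.
- *ANCOVA, with d on the SD of the change score.* The effective effect is d·√(2/(1 + ρ)), so the gain is larger when ρ is low. Power reaches 0.75 for ρ up to about 0.40 at 24 per group and up to about 0.76 at 30 per group.

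**Step 5: consistency within the section.** Back-calculating from 24 per group and 80% power under the stated t-test gives d of about 0.83. This value is derived here and is not printed in the article. Under that test, 24 per group cannot give 80% power only at 0.83 and also more than 75% at 0.65. The primary inputs that the article does print, 2 points with SD 4.5, give d = 2/4.5 = 0.44. That is a separate problem with the primary calculation, and the result in Step 2 does not depend on it.

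**The case against.** The strongest defence is that the sentence on secondary outcomes names no test, and that Section 5.3 plans covariate-adjusted models. With baseline adjustment, power can exceed 0.75 over a sizeable range of correlations, especially at 30 per group. This stands as a limit on the wording: 0.60 and 0.70 are the powers of the unadjusted t-test, not a fixed truth about the planned analysis. It does not rescue the sentence. The article states no correlation, does not say which SD d is scaled to, and names only a t-test in the section where the figure appears. The two scalings also require opposite conditions: a high correlation for one and a low correlation for the other.

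A second objection is that the sentence follows the figure of 30 per group, so 0.70 is the fairer comparison and the gap is about 5 points. That reading is reasonable, but it assumes no dropout straight after the section has allowed for 20%, and it still falls short of 0.75.

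A third is that the primary sample size in the same section does not reproduce either, so the whole section may need rewriting. That is true: a 2-point difference with SD 4.5 has power of about 0.33 at 24 per group. Still, correcting the primary calculation while keeping 60 participants would leave this sentence wrong.

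Finally, the sentence sets no sample size, significance level or decision rule. That is why this is a correction to make and not a flaw in the conduct of the trial.

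**Conclusion.** The point holds. Under the only test stated in Section 2.3, power at d = 0.65 is 0.60 with 24 evaluable per group and 0.70 if all 60 participants are retained, against a claim of more than 0.75. The chance of missing a true effect of that size is about 40% (1 − 0.597) at the planned evaluable number and about 30% (1 − 0.697) with no dropout, where the claim implies less than 25%. This rests on a two-sided 5% t-test with equal groups and no covariate adjustment. An adjusted analysis could reach 0.75, but only under an assumption the article does not state.

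**What to change.** Replace the last sentence of Section 2.3 with text to this effect: with 24 evaluable participants per group, a two-sided 5% t-test has power 0.60 for d = 0.65 (0.70 if all 60 are retained), and power of 0.75 is reached at d = 0.78 (0.69 if all are retained). Drop the description of this power as adequate, and say that the secondary outcomes will be interpreted through their estimates and confidence intervals.

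If the figure relied on baseline adjustment, state instead the assumed correlation, the SD to which d is scaled and the number per group used, and give the power for the unadjusted test alongside. If the primary calculation is revised and the sample size changes, recompute these figures at the new number.

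The cost is one sentence and a less favourable figure. Recruitment, assessments and the planned models are unaffected.
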